## 12.5 Interim Analysis

**Not applicable**

## 12.6 Reporting and Exclusions

### **12.6.1 Evaluation of Toxicity**

Not applicable

### **12.6.2 Evaluation of Response**

All subjects included in the study will be assessed for response to treatment if they have received at least once coaching session after randomization given the intent-to-treat analysis that will be applied.

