### **7.7.1 Dosing Delays/Dose Modifications**

**Not applicable**

## 7.8 General Concomitant Medication and Supportive Care Guidelines

**Not applicable**

## 7.9 Duration of Therapy and Criteria for Removal from Study

All control and treatment group participants will receive the study intervention for 24 weeks. A subject’s follow-up in the study will end after one of the following applies:

- Subject’s voluntary withdrawal
- Subject lost to follow-up
- Adverse medical event in which the participant has been advised to halt all physical activity or needs to initiate a new medically prescribed diet
- Subject death
- Completion of all scheduled study follow-up appointments

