## 7.12 Study Intervention/Follow-up Compliance

Adherence to the protocol will be assessed and verified through the completion of REDCap forms each time that a study team member speaks with participants. This REDCap form will contain questions to verify the date of each coaching session and verify the collection of any related materials (i.e. verify collection of food logs, etc). It is mandatory for study team members to complete the REDCap form and the phone log form as these documents will be used to calculate study intervention compliance.

5 attempts will be made to get participants to return for study follow up appointments via text and calls to the participant. A participant will be considered “lost to follow up” when 3 consecutive sessions have been missed and the study team can no longer get in contact with the participant. Participants that are not lost to follow up will be considered as no longer participating in the study when week 24 of the study (close out interview) has been completed.

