# 8. Study Intervention Discontinuation and Participant Discontinuation/Withdrawal

## 8.1 Discontinuation of Study Intervention

Criteria for discontinuing the study intervention is as follows:

- Cardiovascular, pulmonary, hypoglycemia: Adverse events will be defined as cardiovascular (MI, CVA, death), acute shortness of breath, or hypoglycemia precipitated by changes in dietary intake or the physical activity chosen for the study requiring hospitalization/emergency room visit or a physician office visit. Non-routine office visits for cardiac or pulmonary disease or diabetes are expected and not serious unless they lead to the above events.
- Major depressive episode or anxiety attack: Infrequent likelihood. A participant may become depressed, anxious or severely embarrassed if friends/family/acquaintances find out that the person is participating in and/or not losing weight in the program. Patients have the option of not answering any questions they do not want to. As this is a voluntary study, a participant is free to withdraw from the study at any point if they feel uncomfortable or do not want to continue.
- Medication Side Effects: Infrequent risks. The study does not prescribe medication. Weight loss can cause a change in the dose of medication needed to treat common health conditions such as hypertension, diabetes and thyroid dysfunction. Participants will be required to communicate their participation in the study along with their weight loss to a primary care physician.
- Musculoskeletal: Musculoskeletal injury due to the physical activity chosen for this study resulting in hospitalizations, emergency department visits, or treatment for fracture in any setting will be considered expected serious adverse events. Non-routine office visits for musculoskeletal injury are expected and not serious unless lead to the above events. Temporary minor incapacitation due to muscle soreness is also expected and not serious.

Discontinuation from the social network intervention does not mean discontinuation from the study, and remaining study procedures should be completed as indicated by the study protocol. If a clinically significant finding is identified (including, but not limited to changes from baseline) after enrollment, the investigator or qualified designee will determine if any change in participant management is needed. Any new clinically relevant finding will be reported as an adverse event (AE).

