## 8.2 Participant Discontinuation/Withdrawal from the Study

Participants are free to withdraw from participation in the study at any time upon request.

An investigator may discontinue or withdraw a participant from the study for the following reasons:

- Pregnancy
- Significant study intervention non-compliance
- If any clinical adverse event (AE), laboratory abnormality, or other medical condition or situation occurs such that continued participation in the study would not be in the best interest of the participant
- Disease progression which requires discontinuation of the study intervention
- If the participant meets an exclusion criterion (either newly developed or not previously recognized) that precludes further study participation
- Participant lost to follow-up after several attempts to contact subject to schedule study visit.

The reason for participant discontinuation or withdrawal from the study will be recorded on the Withdrawal Case Report Form (CRF). Subjects who sign the informed consent form and are randomized but do not receive the study intervention will be replaced. Subjects who sign the informed consent form, and are randomized and receive the study intervention, and subsequently withdraw, or are withdrawn or discontinued from the study, will not be replaced.

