## 8.3 Lost to Follow Up

A participant will be considered lost to follow-up if he or she fails to return for 3 scheduled visits and is unable to be contacted by the study site staff.

The following actions must be taken if a participant fails to return to the clinic for a required study visit:

- The site will attempt to contact the participant and reschedule the missed visit within 2 days and counsel the participant on the importance of maintaining the assigned visit schedule and ascertain if the participant wishes to and/or should continue in the study.
- Before a participant is deemed lost to follow-up, the investigator or designee will make every effort to regain contact with the participant (where possible, 3 telephone calls and, if necessary, a certified letter to the participant’s last known mailing address or local equivalent methods). These contact attempts should be documented in the participant’s medical record or study file.
- Should the participant continue to be unreachable, he or she will be considered to have withdrawn from the study with a primary reason of lost to follow-up.

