### **12.4.2 Analysis of Secondary Endpoints**

We will examine summary statistics, histograms, and scatter plots of the measured covariates and outcomes for outliers and data trends. Analyses of differences between those completing and not completing the study and the within-group changes during the intervention will be performed according to modified intention-to-treat principles. Multivariate linear regression (MLR) models will be used to examine the relationship between changes in the social network processes and exposure (the social network lifestyle intervention vs the lifestyle intervention), adjusted for covariates selected from univariate analyses; potential covariates for MLR are categorized by theoretical construct. We will also explore the effect of gender by including a three-way interaction (gender*social support*weight loss), although we recognize that we might not have enough power to detect such interactions.

To further explore the effect of the intervention, we will do sensitivity analysis: (1) Multivariable linear regression using weight loss as continuous outcome variables (a change in weight and percent weight change), adjusting for baseline covariates distributed differently between intervention groups; (3) test interaction terms between treatment group and other covariates; and (4) examine completers only.

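### The set called intent-to-treat requires a session after randomisation, untreated randomised subjects are replaced, and the follow-up rules conflict

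*Protocol*

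**What the plan says.** **Analysis set.** Protocol section 12.6.2 assesses subjects for response "if they have received at least once coaching session after randomization given the intent-to-treat analysis that will be applied". Section 12.4.2 says that comparisons of completers with non-completers, and within-group changes, "will be performed according to modified intention-to-treat principles". It does not define that term. The between-arm analysis in the same section is a regression "to examine the relationship between changes in the social network processes and exposure", with no analysis set attached. Completers only is listed as a sensitivity analysis.

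**Replacement.** Section 8.2 replaces subjects who consent and are randomised but do not receive the study intervention. Those who receive it and later leave are not replaced.

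**Follow-up.** Section 7.9 says that follow-up will end on any of several events, among them "Adverse medical event in which the participant has been advised to halt all physical activity or needs to initiate a new medically prescribed diet". Section 8.1 says "Discontinuation from the social network intervention does not mean discontinuation from the study" and asks for the remaining procedures to be completed. Section 7.10 follows subjects for six months after removal. Section 8.2 lets an investigator withdraw a participant from the study for "Significant study intervention non-compliance".

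**Loss to follow-up.** In section 7.12 a participant is lost "when 3 consecutive sessions have been missed" and contact has failed, with five attempts by text and call. In section 8.3 a participant is lost who "fails to return for 3 scheduled visits" and cannot be reached, with three telephone calls and, if needed, a certified letter.

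**The concern.** Intent-to-treat analysis keeps every randomised subject in the assigned arm, because only that set is balanced by design. Attending a first session and receiving the intervention both happen after randomisation. Participants cannot be blind to their arm, and those in the intervention arm must bring in people they know. A set filtered on attendance and topped up by replacement is therefore no longer the randomised set.

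The follow-up conflict matters for a different reason. Staff cannot tell from the protocol whose week-24 weight and survey to pursue after an adverse event, poor compliance or a run of missed visits. An outcome that was never sought cannot be recovered at analysis.

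The secondary between-arm comparisons are at stake: social network processes, behaviour and weight. The stopping-rules text in section 15 says that one goal is to obtain estimates for a larger trial, so a biased difference would be carried into that trial's planning.

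**Working it through.** **1. Who is in the set.** Section 12.6.2 needs at least one session after randomisation, so never-starters are out. Section 8.2 then replaces randomised subjects who did not receive the intervention, so the number randomised can exceed 132. Neither rule is compatible with the label intent-to-treat. How many people are affected is not stated.

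**2. Follow-up rules side by side.**
- Section 7.9: follow-up ends on the listed adverse events.
- Section 8.1: stopping the intervention is not leaving the study, and procedures continue.
- Section 7.10: follow-up runs six months past removal.
- Section 8.2: removal from the study for non-compliance is allowed but not required.

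The first three cannot all be followed for a participant who stops because of an adverse event.

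**3. The plan's own power figures.** Inputs from section 15: 132 randomised (66 per arm), difference 8 lb, SD 10.4. Two-sided alpha of 0.05 is assumed, as none is stated. With n = 66 × (1 − dropout) and SE = 10.4 × √(2/n), power = Φ(8/SE − 1.96).

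| Dropout | n per arm | Computed | Stated |
|---|---|---|---|
| 15% | 56 | 98.3% | 98% |
| 30% | 46 | 95.8% | 96% |
| 40% | 39 | 92.5% | 92% |
| 50% | 33 | 87.8% (86.8% by noncentral t) | 88% in the table, 0.87 in the text |

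The figures reproduce, on retained subjects only. The power statement is not at fault.

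**4. Possible bias.** Suppose there is no true effect, shares x (intervention) and y (control) are left out, and in both arms those left out lose k lb less than those retained. Then bias b = (x − y) × k. With SE = 10.4 × √(1/n1 + 1/n2), n1 = 66(1 − x) and n2 = 66(1 − y), the type I error is Φ(−1.96 + b/SE) + Φ(−1.96 − b/SE). All of x, y and k are assumptions.

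| x vs y | k = 5 lb | k = 8 lb | k = 10.4 lb |
|---|---|---|---|
| 15% vs 15% | 0 lb, 5.0% | 0 lb, 5.0% | 0 lb, 5.0% |
| 10% vs 5% | 0.25 lb, 5.2% | 0.40 lb, 5.5% | 0.52 lb, 5.9% |
| 15% vs 5% | 0.50 lb, 5.8% | 0.80 lb, 7.0% | 1.04 lb, 8.5% |
| 30% vs 15% | 0.75 lb, 6.5% | 1.20 lb, 8.9% | 1.56 lb, 11.7% |

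Worked case, 15% vs 5% with k = 8: b = 0.10 × 8 = 0.80; n1 = 56.1, n2 = 62.7, SE = 1.91; b/SE = 0.42; Φ(−1.54) + Φ(−2.38) ≈ 0.070.

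**5. What analysing everyone costs.** With 66 per arm and the full 8 lb, SE = 10.4 × √(2/66) = 1.81 and power is 99.3%. If a share of the intervention arm is kept in but gains nothing extra, the difference shrinks:
- 5%: 8 × 0.95 = 7.6 lb, power 98.7%.
- 10%: 8 × 0.90 = 7.2 lb, power 97.8%.
- 15%: 8 × 0.85 = 6.8 lb, power 96.4%.

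**The case against.** **The one-session rule may exclude few people.** Sections 4.2 and 6.1.2 support this. Every index participant must be able to name a participating network member before randomisation, the week 1 and week 2 sessions are the same in both arms, and the first arm-specific session is week 3. This stands in part. Arm-dependent non-starting remains plausible, because the Protocol Summary has network members nominated, consented and interviewed at baseline, but it is not quantified.

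**Removal for non-compliance is discretionary.** Section 7.11 also says that the principal investigator and co-investigators are blinded. The discretion stands. The blinding is weaker protection than it looks, since section 15 sends unblinded adverse event data to the principal investigator.

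**Both loss-to-follow-up rules also require failed contact.** This stands: the difference in wording does not by itself end pursuit of someone who can be reached.

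A reader might also infer more than the protocol supports:
- *That withdrawals inflate retention.* Section 12.4.1 divides by those who completed the baseline assessment, so a withdrawn participant stays in the denominator as a non-completer and lowers the rate.
- *That withdrawing poor attenders lifts the 75% attendance result.* No text removes them from that denominator, and anyone who attended some sessions after randomisation meets the one-session rule. The section simply does not say that they stay in.
- *That the main comparison is one of compliers.* Completers only is a sensitivity analysis, so the main set is wider.
- *That section 12.4.2 gives the section 12.6.2 set a second name.* The modified intention-to-treat phrase is attached to completer comparisons and within-group changes, not to that set or to the between-arm regression.

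**Conclusion.** The concern holds for the label, the replacement rule and the conflicting follow-up text. Together they depart from analysis as randomised in a trial whose participants know their arm. It should be fixed, but it does not undermine the trial: the primary endpoints are feasibility targets, and the exposure is in the secondary between-arm comparisons.

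The size cannot be derived from the protocol. Over the assumed range, bias runs from zero (equal loss, same retained-versus-lost gap in both arms) to 1.56 lb with a type I error of 11.7% (30% versus 15% lost, gap 10.4 lb). These figures assume that those left out have no week-24 weight in the analysis. Missing-data methods may sit in a statistical analysis plan that is not shown and could reduce the bias. They could not restore assessments that were never attempted.

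**What to change.** - In sections 12.4.2 and 12.6.2, define the main between-arm set as everyone randomised, including any who are replaced, analysed as randomised. Keep at least one session, and completers, as sensitivity sets. Drop the intent-to-treat label from the one-session rule.
- In section 12.4.1, state that withdrawn participants stay in the attendance denominator.
- In section 8.2, separate stopping sessions from leaving the study, so that non-compliance alone does not end outcome collection.
- Reconcile sections 7.9, 7.10 and 8.1, and sections 7.12 and 8.3, so that the week-24 assessment is sought from everyone who has not withdrawn consent. Clinical handling after an adverse event stays with the investigators.

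The cost is protocol wording, some extra week-24 contacts and possibly a slightly smaller effect estimate. As shown above, little power is lost.

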# 13. Adverse Event Reporting Requirements

Adverse event (AE) monitoring and reporting is a routine part of every clinical trial. The investigator will be required to provide appropriate information concerning any findings that suggest significant hazards, contraindications, side effects, or precautions pertinent to the safe use of the drug or device under investigation. Safety will be monitored by evaluation of adverse events reported by subjects or observed by investigators or research staff, as well as by other investigations such as clinical laboratory tests, x-rays, electrocardiographs, etc.

## 13.1 Adverse Event Definition

An adverse event (also referred to as an adverse experience) can be any unfavorable and unintended sign (e.g., an abnormal laboratory finding), symptom, or disease temporally associated with the use of a drug, and does not imply any judgment about causality. An adverse event can arise with any use of the drug (e.g., off-label use, use in combination with another drug) and with any route of administration, formulation, or dose, including an overdose.

### **13.1.1 Investigational Agent or Device Risks (Expected Adverse Events)**

Expected adverse events that could result from people receiving the intervention include:

Cardiovascular, pulmonary, hypoglycemia: Adverse events will be defined as cardiovascular (MI, CVA, death), acute shortness of breath, or hypoglycemia precipitated by changes in dietary intake or the physical activity chosen for the study requiring hospitalization/emergency room visit or a physician office visit. Non-routine office visits for cardiac or pulmonary disease or diabetes are expected and not serious unless they lead to the above events.

Major depressive episode or anxiety attack: Infrequent likelihood. A participant may become depressed, anxious or severely embarrassed if friends/family/acquaintances find out that the person is participating in and/or not losing weight in the program. Patients have the option of not answering any questions they do not want to. As this is a voluntary study, a participant is free to withdraw from the study at any point if they feel uncomfortable or do not want to continue.

Medication Side Effects: Infrequent risks. The study does not prescribe medication. Weight loss can cause a change in the dose of medication needed to treat common health conditions such as hypertension, diabetes and hypothyroidism. Participants will be required to communicate their participation in the study along with their weight loss to a primary care physician.

Musculoskeletal: Musculoskeletal injury due to the physical activity chosen for this study resulting in hospitalizations, emergency department visits, or treatment for fracture in any setting will be considered expected serious adverse events. Non-routine office visits for musculoskeletal injury are expected and not serious unless lead to the above events. Temporary minor incapacitation due to muscle soreness is also expected and not serious.

### **13.1.2 Adverse Event Characteristics and Related Attributions**

During the conduct of this study, we will use the WCM Data Safety Monitoring Committee Adverse Event reporting system.

**WCM grade:**

- **Attribution** of the AE:
  - Definite – The AE *is clearly related* to the study treatment.
  - Probable – The AE *is likely related* to the study treatment.
  - Possible – The AE *may be related* to the study treatment.
  - Unlikely – The AE *is doubtfully related* to the study treatment.
  - Unrelated – The AE *is clearly NOT related* to the study treatment.

### **13.1.3 Recording of Adverse Events**

All adverse events will be recorded on a subject specific AE log. The AE log will be maintained by the research staff and kept in the subject’s research chart.

### **13.1.4 Reporting of AE to WCM IRB**

All AEs occurring on this study will be reported to the IRB according to the IRB policy, which can be accessed via the following link: <http://researchintegrity.weill.cornell.edu/forms_and_policies/forms/Immediate_Reporting_Policy.pdf>.

### **13.1.5 Reporting Events to Participants**

**Not applicable**

### **13.1.6 Events of Special Interest**

**Not applicable**

### **13.1.7 Reporting of Pregnancy**

Participants must report any instance of pregnancy, in which they will be removed from the study.

## 13.2 Definition of SAE

SAEs include death, life threatening adverse experiences, hospitalization or prolongation of hospitalization, disability or incapacitation, overdose, congenital anomalies and any other serious events that may jeopardize the subject or require medical or surgical intervention to prevent one of the outcomes listed in this definition.

### **13.2.1 Reporting of SAE to IRB**

All SAEs occurring on this study will be reported to the IRB according to the IRB policy, which can be accessed via the following link:

<http://researchintegrity.weill.cornell.edu/forms_and_policies/forms/Immediate_Reporting_Policy.pdf>.

### **13.2.2 Reporting of SAE to FDA [For Protocols Where WCMC is the Sponsor-Investigator]**

**Not applicable**

### **13.2.3 Reporting of SAE to <*Insert Pharmaceutical Company Name>***

**Not applicable**

##

## 13.3 AE/SAE Follow Up

All SAEs and AEs reported during this study will be followed until resolution or until the investigator confirms that the AE/SAE has stabilized and no more follow-up is required. This requirement indicates that follow-up may be required for some events after the subject discontinues participation from the study.

## 13.4 Time Period and Frequency for Event Assessment and Follow Up

The occurrence of an adverse event (AE) or serious adverse event (SAE) may come to the attention of study personnel during study visits and interviews of a study participant presenting for medical care, or upon review by a study monitor.

All AEs including local and systemic reactions not meeting the criteria for SAEs will be captured on the appropriate case report form (CRF). Information to be collected includes event description, time of onset, clinician’s assessment of severity, relationship to study product (assessed only by those with the training and authority to make a diagnosis), and time of resolution/stabilization of the event. All AEs occurring while on study must be documented appropriately regardless of relationship. All AEs will be followed to adequate resolution.

Any medical condition that is present at the time that the participant is screened will be considered as baseline and not reported as an AE. However, if the study participant’s condition deteriorates at any time during the study, it will be recorded as an AE.

Changes in the severity of an AE will be documented to allow an assessment of the duration of the event at each level of severity to be performed. AEs characterized as intermittent require documentation of onset and duration of each episode.

Study team members will record all reportable events with start dates occurring any time after informed consent is obtained until 7 (for non-serious AEs) or 30 days (for SAEs) after the last day of study participation. At each study visit, the investigator will inquire about the occurrence of AE/SAEs since the last visit. Events will be followed for outcome information until resolution or stabilization.

